### Outcome measures

Primary outcome measures for the infant will be derived from the overnight sleep study (amount of time head covered, amount of time in thermal comfort zone, number of hypoxic events and amount of time in the sleep device) and from surveys (full or exclusive breastfeeding at 3 and 6 months). Secondary outcomes identified from the sleep study include number of infant head covering events, number of parental (non-feed related) touching infant events, amount of time in the prone sleep position, the number of behavioural arousals, and the amount of time infant is awake overnight.

Psychosocial factors will also be measured. Using questionnaires, maternal environmental chaos will be measured at baseline. Social support, and social and economic stress will be measured at baseline and 3 months. Maternal depression and change in depression (from baseline) will be measured at 3 months and 6 months. Parenting factors, including beliefs about infant care, attachment, and parenting adaptation will be measured at baseline and 3 months using both the questionnaires and maternal salivary oxytocin levels at baseline, 1 month and 3 months. Maternal mind-mindedness will be measured at baseline, 3 and 6 months, using the questionnaires, and an audio recording of the mother talking about her baby (see Table 
1).

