### Sample size

Our previous studies comparing bed-sharing to cot-sleeping infants
[49, 50] have been used to determine sample size using two of our primary outcome measures. The third major outcome (breast-feeding proportion) is derived from national data on breast-feeding (full or exclusive) by ethnicity
[51].

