### Head covering

The proportion of babies having an overnight sleep with a head covering episode by blankets was 1/37 and so, in order to detect a difference of 15% between babies sleeping in wahakura and cots with 80% power using the 5% level of significance, two groups of 88 babies would be needed.

Assuming the proportion of babies having an overnight sleep with a head-covering episode by blankets will be 3% when sleeping in a bassinette, 88 babies per group are required to detect a difference of 15% between babies sleeping in wahakura and cots with 80% power using the 5% level of significance.

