### Total numbers required

Overall, we believe that we should aim to recruit enough babies so that we have complete data at 1 month, of 100 babies per group – i.e. enrol 105 babies per group.

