### Measures

#### Sleep studies

A formal home sleep study will be completed when babies are 1 month old. After negotiation with the family, a researcher will visit the home in the evening, and set up the equipment for recording. We plan to use the minimum possible equipment, with the least possible attachments to the baby. Infrared video using a Swann wireless ADW-400 digital camera and recorder, and oximetry using a Massimo Rad 8 set to a 2 second averaging time (analysed using Visi-Download software) will be recorded. Four temperature probes will be used to measure infant toe and core temperature (measured over the liver) and room and outside temperature, using a flat film RTD temperature sensor (5×2 mm). Temperature will be recorded onto GP-HR general purpose 4 channel logger to be attached to the Massimo oximeter.

Video recordings will be viewed off-line using Noldus Observer XT, a software package for the collection, analysis, and presentation of observational data. The data will be coded according to a taxonomy adapted from that used in the Durham University Parent-Infant Sleep Lab (personal communication, [name], Parent-Infant Sleep Lab, Durham University; June 2012). Key categories will include infant sleep time, infant awake time, behavioural arousals, head covering events, breastfeeding events, infant sleep position, and maternal interactions. The software allows synchronisation with physiological recordings of oxygen saturation and temperature. Hypoxic events will be defined as decreases to <90% lasting >10 seconds. Infant peripheral temperature will be used as an indicator of thermal comfort. On the basis of our previous studies
[49] we decided to use a peripheral temperature of <34 degrees as indicating cold stress, or >36 degrees as indicating heat stress. The data will be analysed to identify behavioural events associated with hypoxic episodes or changes in infant temperature.

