#### Data analysis

The data will be analysed using modified intention to treat, including only those who completed at least one of the 1, 3 or 6 month visits. Chi-squared tests or Student t-tests will be used to compare the outcomes in the two groups. A per protocol analysis will also be carried out to estimate differences in the outcome variables in those who were compliant with the sleeping arrangement to which they were assigned.

This study will also provide an opportunity to examine factors associated with breastfeeding and sleep practices in a disadvantaged group. The breastfeeding data will be analysed using a discrete time model.

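### Head covering is declared primary as minutes but sized as a yes/no proportion, so the stated 80% power does not belong to the declared outcome; comfort-zone time has the same mismatch

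*Protocol article*

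**What the plan says.** Under Outcome measures, the primary outcomes from the overnight study are "amount of time head covered, amount of time in thermal comfort zone, number of hypoxic events and amount of time in the sleep device": three durations and a count.

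The Sample size section says that earlier studies "have been used to determine sample size using two of our primary outcome measures". The subsection on head covering then works with a binary quantity: "The proportion of babies having an overnight sleep with a head covering episode by blankets was 1/37". It assumes that the proportion with a "head-covering episode by blankets will be 3% when sleeping in a bassinette", and concludes that "88 babies per group are required to detect a difference of 15% between babies sleeping in wahakura and cots with 80% power". The Temperature control subsection also counts babies: 75% of cot sleepers were in the comfort zone, and 98 per group would detect a 20% difference. The overall target is "complete data at 1 month, of 100 babies per group – i.e. enrol 105 babies per group".

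The Data analysis section states: "Chi-squared tests or Student t-tests will be used to compare the outcomes in the two groups". It does not say which outcome gets which test.

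The first hypothesis, under Overall study design, is that the two devices do not differ significantly on several measures, including the length of head covering and the thermal environment.

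**The concern.** Three parts of the protocol should describe one quantity and do not. The outcome list has minutes covered, the sample size has whether a baby was covered at all, and the analysis section names two tests of which only the t-test can take minutes as they stand. The yes/no quantity is neither a primary nor a secondary outcome; the nearest secondary outcome is the number of head-covering events.

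If few babies are covered, minutes are mostly zeros with a right tail. A t-test on such data can have much less power than a comparison of proportions in the same babies. Head covering is a central hazard here, and the trial is meant to inform whether the device can be recommended. With a hypothesis of no significant difference, a test weaker than advertised makes the reassuring answer more likely.

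**Working it through.** **1. What the sample size is for.** For two proportions, n = [z(α/2)·√(2p̄q̄) + z(β)·√(p1q1 + p2q2)]² / (p2 − p1)².

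- Head covering: p1 = 0.03, p2 = 0.18 (15 percentage points), two-sided 5% assumed, 80% power. With p̄ = 0.105: n = [1.960·√0.18795 + 0.8416·√0.1767]² / 0.15² = (0.850 + 0.354)² / 0.0225, giving 65 per group, or 78 with continuity correction.
- The stated 88 is not reproduced. It is close to 3% against 15% (89 uncorrected). For 15 points it errs on the large side: the formula gives power 0.91 at 88 and 0.94 at 100 per group.
- Comfort zone: 75% against 55%, with continuity correction, gives 98, which matches the protocol.

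Both calculations are for proportions of babies. Neither uses a mean or SD of minutes, and the protocol gives none.

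**2. Share of zeros.** 1/37 = 2.7%, taken as 3%. If this blanket rate carries over to the primary outcome, 97% of bassinet values are zero. In the wahakura arm the share is 82% (target 18%) or 85% (target 15%).

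**3. Why minutes cost power.** Let covered babies have mean duration m and coefficient of variation CV, equal in both arms. The mean difference is m(p2 − p1). The variance per baby is m²[p(1 + CV²) − p²]. At 100 per group, in units of m:

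- CV 0: SE = √[(0.0291 + 0.1476)/100] = 0.042; 0.15/0.042 = 3.57.
- CV 1: SE = √[(0.0591 + 0.3276)/100] = 0.062; 0.15/0.062 = 2.41.
- CV 2: SE = √[(0.1491 + 0.8676)/100] = 0.101; 0.15/0.101 = 1.49.

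The signal is fixed while the noise grows with the spread of durations. A normal approximation from these ratios is too pessimistic for skewed data (0.67 at CV 1, against 0.80 simulated), so simulation is used below.

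**4. Simulated power.** Minutes are zero with probability 1 − p and otherwise log-normal, with the same distribution in both arms (assumed). Rates are 3% and 18%; CV = √(exp(log-SD²) − 1).

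| log-SD | CV | t-test, 100 per group | t-test, 88 per group |
|---|---|---|---|
| 0.5 | 0.53 | 0.90 | not tabulated (0.88 at CV 0.5) |
| 0.8 | 0.95 | 0.82 | 0.77 |
| 1.0 | 1.31 | 0.73 | 0.66 |
| 1.2 | 1.79 | 0.63 | 0.58 |
| 1.5 | 2.91 | 0.48 | 0.44 |

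Comparing proportions in the same simulated babies at 100 per group gives about 0.96 throughout. Independent runs of the t-test agree to within about 0.01.

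**5. Sensitivity.**

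- Target 3% against 15%, log-SD 1.0, 100 per group: t-test about 0.58, proportions 0.89.
- CV 1, 100 per group: if wahakura episodes last twice as long on average, t-test power rises to 0.95; if half as long, it falls to 0.51.
- 3% in both arms, log-SD 1.0: the t-test rejects about 1.5% of the time, well under its nominal 5%.

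**The case against.** Several counter-arguments carry weight.

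- **No test is assigned to an outcome.** A chi-squared test on any against no covering is compatible with the text, and it can be derived from the secondary count of events. This stands, but that test would address an outcome the protocol does not declare. An unseen SAP could choose the test; it would not make the published outcome list and sample size agree.
- **The 1/37 is for blankets only.** The primary outcome has no such limit, and the Breastfeeding section also records covering during feeds. This stands: the share of zeros may be lower than 97%, so the simulation is conditional on the rate carrying over.
- **The loss of power rests on an assumed spread.** This stands too. A reader might infer that the trial has far less power than stated. The documents do not show that: at 100 per group and 15 points, power is about 80% or more while the CV is about 1 or less, and it changes if durations differ between arms.
- **Saying that one or two babies would decide the t-test is too strong.** Under 3% against 18%, the largest value was typically 16–30% of all minutes; it was 37–53% with both arms at 3%.

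A reader might also extend the point to hypoxic events, as mostly zeros and sized as proportions. The documents do not support this. They give only a definition ("Hypoxic events will be defined as decreases to <90% lasting >10 seconds"), with no rate, effect size or sample size. Adjustment for recording length and the choice of interval method are ordinary SAP detail. Treating non-significance as safety is a separate weakness that would remain under any test unless a margin were set.

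**Conclusion.** The mismatch is certain on the face of the protocol. Head covering and comfort-zone temperature are declared as time and sized as proportions of babies. The 80% figure belongs to quantities that are not declared outcomes.

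The size of the consequence is uncertain. For head-covered minutes, power is unknown; it is materially below 80% if durations are skewed (0.73 to 0.48 for log-SD 1.0 to 1.5 at 100 per group) and at or above 80% if they are not (0.90 to 0.82 for log-SD 0.5 to 0.8). These figures assume log-normal durations, equal distributions in both arms, rates of 3% and 18%, and a blanket rate that applies to all head covering. No corresponding figure can be given for comfort-zone time, as the protocol reports no distribution for it. The direction matters more than the exact value: under a hypothesis of no significant difference, lost power favours a conclusion of safety.

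**What to change.** Make outcome, sample size and test refer to the same quantity.

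- Declare any head covering during the recorded night as the confirmatory head-covering outcome. Say whether it is limited to blankets, since the 3% is; if not, restate the bassinet rate.
- Compare the arms by a risk difference with 95% CI, and use an exact test if expected counts are small. At 3% in both arms of 100, only 3 babies per arm would be expected to be covered.
- Keep minutes covered as supporting evidence, with a permutation test and a bootstrap CI for the mean difference.
- Treat the comfort zone the same way: declare the proportion of babies in the zone as confirmatory, with time in the zone as support.
- If the durations are to stay confirmatory, state plainly that the 80% power does not apply to them.

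The cost is wording and standard software, with no extra data or babies; the change should be made before any comparison by arm. The drawback is that a yes/no outcome treats a brief covering and a long one alike, which is why minutes should still be reported.

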### Contamination

There may be contamination with those assigned to one condition deciding to obtain and use the other type of sleeping device. We will check the degree of contamination by identifying this at the 1 month sleep study, and by asking at each time point about use of other sleep devices. For safety analyses (head covering, peripheral temperature and oxygen saturation), analysis will be by actual device used. For breast-feeding results, both the intention to treat and actual sleep device used will be analysed.

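### Outside temperature is logged on each study night, but the primary thermal outcome is compared only by unadjusted tests, which leaves weather as noise and could blur effects that differ between cold and warm nights

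*Protocol article*

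**What the plan says.** All references are to the protocol article.

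- **Outcome measures** lists as primary outcomes from the sleep study, among others, "amount of time in thermal comfort zone, number of hypoxic events and amount of time in the sleep device".
- **Sleep studies** gives each baby one study: "A formal home sleep study will be completed when babies are 1 month old". The equipment includes weather measurement: "Four temperature probes will be used to measure infant toe and core temperature (measured over the liver) and room and outside temperature".
- The same section sets limits on both sides: "we decided to use a peripheral temperature of <34 degrees as indicating cold stress, or >36 degrees as indicating heat stress".
- **Data analysis** names the between-group comparison: "Chi-squared tests or Student t-tests will be used to compare the outcomes in the two groups". No covariate, season term or device-by-temperature term is named. The section does name a model for breastfeeding (discrete time).
- The only other stated use of the temperature data is in **Sleep studies**: "The data will be analysed to identify behavioural events associated with hypoxic episodes or changes in infant temperature". Weather is not mentioned there.
- **Contamination** adds: "For safety analyses (head covering, peripheral temperature and oxygen saturation), analysis will be by actual device used".
- The first hypothesis under **Overall study design** is that the two devices do not differ significantly in thermal environment.

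**The concern.** With one night per baby, the weather on that night is an obvious candidate source of variation in toe temperature between babies. Outside temperature is measured, and allocation cannot affect it, so it is a safe covariate. The stated tests ignore it.

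The second issue is the shape of the outcome. Both cold and heat take a baby out of the zone. A device that keeps babies warmer could therefore bring some into the zone on cold nights and push others out on warm nights. A single pooled difference is the net of the two. Because the hypothesis is one of no significant difference, a small net difference could be read as reassurance.

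Third, the thermal comparison is to be made by the device actually used. Randomisation does not protect that comparison, and if families choose a device partly by the weather, outside temperature is a confounder.

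**Working it through.** **1. The plan's own figure.** Temperature control states 98 babies per group to detect a 20-point difference from 75%, with 80% power at the 5% level. For 75% v 55%, two-sided and continuity-corrected, the two-proportion formula gives 98 (89 without the correction). The figure reproduces and is not in dispute. It sizes a proportion of babies in a zone defined relative to core temperature, whereas the primary outcome is a duration and Sleep studies uses absolute limits of 34 and 36 degrees. It therefore says nothing about the SD of the outcome or about weather.

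**2. Precision.** Let R² be the share of outcome variance explained by outside temperature. The documents do not give it; 5–30% is an assumption. For a comparison with 80% power unadjusted (two-sided 5%):

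- sample-size multiplier = 1/(1 − R²)
- power = Φ[(1.960 + 0.842)/√(1 − R²) − 1.960]

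| R² | Multiplier | Power |
|---|---|---|
| 0.05 | 1.05 | 82% |
| 0.10 | 1.11 | 84% |
| 0.20 | 1.25 | 88% |
| 0.30 | 1.43 | 92% |

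At R² = 0.05: 2.802/0.975 − 1.960 = 0.915, and Φ = 0.82. At R² = 0.30: 2.802/0.837 − 1.960 = 1.389, and Φ = 0.92.

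**3. Opposite effects, in a worked illustration.** All inputs are assumed: outside temperature uniform from 4 to 24 °C, toe temperature rising 0.1 °C per 1 °C outside, a device adding 0.7 °C, SD 0.9 °C, zone 34–36 °C, one temperature scored per night. The result also depends on the control group's mean toe temperature at 14 °C outside, so two values are shown (control v warmer device).

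| | Mean 34.55 °C | Mean 35.0 °C |
|---|---|---|
| In zone, all nights | 60.5% v 63.3% | 64.5% v 55.3% |
| In zone, below 10 °C outside | 43% v 67% | 60% v 72% |
| In zone, above 18 °C outside | 71% v 50% | 60% v 33% |
| Above 36 °C, all nights | 9% v 24% | 18% v 39% |

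The opposite directions appear in both columns. Near-complete cancellation appears only in the first.

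**4. Power when effects oppose.** Assume 75% in zone, ±20 points on cold and warm nights, and 100 per group (the protocol's target for complete data at 1 month). The pooled difference is 20 × (share cold − share warm). With 50, 60, 70 and 80% warm nights it is 0, −4, −8 and −12 points, with power of about 5, 9, 24 and 45%. A uniform −20 has 85%.

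For the group-by-weather contrast with 50 babies per cell, power = Φ(2e/√v − 1.96), where v is the sum of p(1 − p)/50 over the four cells. For e = 0.20, v = 0.67/50 = 0.0134 and power is 93%. It is 71% for e = 0.15 and 38% for e = 0.10.

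**5. Time in zone, simulated.** Assumed: 100 per group, between-infant SD 0.7, weather slope 0.6 degrees per SD, device 0.5 degrees warmer. Figures are rejection rates.

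| Position of the arms | t-test | Linear weather covariate | Group-by-weather term |
|---|---|---|---|
| Evenly about mid-zone | 5% | 5% | 68% |
| Control at mid-zone | 23% | 25% | 66% |
| Control at 35.5 | 82% | 90% | 38% |

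A linear covariate helps when the control arm sits off-centre, but it does not reveal opposite effects when the arms straddle the middle of the zone.

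**The case against.** The strongest reply is that nothing here is wrong. An unadjusted test between randomised groups is valid, covariates are often left to an analysis plan, and a one-sentence statement covering all outcomes does not rule out further models. The validity point stands in full. The rest stands in part: an analysis plan may add a model, but the article does name a method for this outcome, and a better one is available from data already collected.

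Four stronger readings are tempting, and the documents do not support them.

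- *That weather adjustment would buy a large gain, with R² up to 40%.* The outcome is time in a two-sided zone, which does not rise steadily with temperature. In the illustration, a quadratic in outside temperature explains only about 2–11% of in-zone variance. In the time-in-zone simulation, a linear term explains about 2% of control-arm variance at mid-zone and 15% off-centre. Other assumed within-night SDs gave about 5–39%. The top of that range is optimistic.
- *That opposite effects are in fact averaged away.* No weather slope, device warming effect or spread of outside temperature is given. Near-cancellation in the illustration needs a control mean of about 34.55 °C; at 35.0 °C the pooled difference is about −9 points.
- *That overheating would be hidden.* In the same illustration, toe temperature above 36 °C rises from about 9% to 24% pooled over all nights, and an unadjusted comparison with 100 per group has roughly 83–85% power for that. Much of the loss comes from merging two tails into one zone, and separate reporting of the tails addresses it without any weather data.
- *That adjustment would rescue the analysis by device used.* Weather-driven choice of device is possible but not documented, and one covariate does not replace randomisation.

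**Conclusion.** The point holds as a cheap improvement to the stated method. It does not show an invalid analysis. Outside temperature is recorded, allocation cannot affect it, and no stated comparison uses it.

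Between randomised groups the cost is precision and information, with no bias. On an assumed R² of 5–30%, 80% power would become about 82–92%; the true gain is unknown. Because the zone is two-sided, the pooled difference could understate effects that run in opposite directions on cold and warm nights. Whether such effects exist, and how fully they would cancel, depends on values not in the documents. In the analysis by device used, outside temperature is a possible confounder as well, and adjusting for it would help with that one factor only.

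**What to change.** In Data analysis:

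1. Compare time in the thermal comfort zone by regression on group plus mean outside temperature that night. Use a quadratic or spline term, because comfort can fall at both extremes, and robust standard errors.
2. Do not adjust for room temperature, which may depend on where the baby sleeps.
3. Report time below 34 degrees and time above 36 degrees separately by group.
4. As a prespecified secondary analysis, report the group-by-outside-temperature term.

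The cost is a change of wording, a few degrees of freedom, and a rule for nights when the outside probe fails, such as filling in from local weather data. The interaction has limited power (about 38% for ±10 points under the assumptions above), so a non-significant term should not be read as evidence that the device effect is the same on cold and warm nights. No extra participants or measurements are needed.

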## Discussion

As far as we are aware, there are no other studies of this nature being performed anywhere in the world. SUDI prevention is an important area of research in the Western world, and the advent of ongoing, extremely high rates of SUDI in communities of deprivation, including indigenous communities, has not been effectively addressed to date. In addition, the *wahakura* has not been developed by the scientific community, nor has it arisen from the wider health sector. It is a cultural reclamation of an item used traditionally in Māori society in the effort to continue the valued practice of bedsharing, while maintaining the safety of the infant. We will assess the risks and benefits around the *wahakura*, to establish whether it might be able to be recommended as a safe sleeping device for prevention of SUDI. Whilst it has been suggested there is some ‘face validity’
[61] and there is support in the high risk community for this device, there is no empirical evidence as yet assessing its safety. This study seeks to provide exactly that.
